## Abstract

**Background:**

Labor is induced in over 20% of women in France. Prostaglandins, especially intravaginal dinoprostone (Propess®), are widely used to initiate cervical ripening. If labor does not start within 24 h, there is uncertainty about whether to administer a second dinoprostone pessary or to use oxytocin to induce labor in order to achieve a vaginal delivery.

**Methods:**

RE-DINO is a prospective, open-label, multicenter, randomized superiority trial with two parallel arms running in six French hospitals. A total of 360 patients ≥ 18 years of age at > 37 weeks of gestation who exhibit unfavorable cervical conditions (Bishop score < 6) 24 h after placement of the first Propess®, with fetuses in cephalic presentation, will be included. Patients with premature membrane rupture, uterine scars, or multiple pregnancies will be excluded. Our principal objective is to determine whether placement of a second Propess® (followed by oxytocin [Syntocinon®], if necessary) in women for whom the first Propess® failed to induce cervical ripening increases the vaginal delivery rate compared to direct oxytocin injection. The vaginal delivery rate is therefore the primary outcome. The secondary outcomes are the induction failure rates and maternofetal morbidity and mortality.

**Discussion:**

This study may help in determining the optimal way to induce labor after failure of a first Propess®, an unresolved problem to date. This trial explores the effectiveness and safety of placing a second Propess® and may contribute to development of an obstetric consensus.

**Trial registration:**

Registered on 2 September 2016 at clinicaltrials.gov (identification number NCT02888041).

## Background

Perinatal surveys indicate that labor is induced in more than 20% of French women [1, 2]. Prostaglandins (PGs) [usually intravaginal dinoprostone (Propess®)] are widely used to initiate cervical ripening [3, 4].

The labor induction rate following placement of a single Propess® is 65–73%, with more than 80% of subsequent deliveries being vaginal [5, 6]. Currently, patients who have not entered labor 24 h after placing a Propess® are either induced by oxytocin (Syntocinon®) [7–9] or undergo cesarean section. Alternatively, a second Propess® is placed in several maternity hospitals [10] to reduce the rate of cesarean section (20.4% in France) [11]. A non-comparative retrospective monocentric study in 111 patients showed that placement of a second Propess® was associated with a vaginal delivery rate of 53.1% and no additional maternofetal morbidity or mortality [12]. Antonazzo et al. [13] performed a randomized trial with low patient numbers; the vaginal delivery rate was higher when a second Propess® was placed than when labor was induced by oxytocin. However, in the absence of a marketing authorization for use of a second Propess®, a prospective assessment is required.

Labor induction features medical stimulation of uterine contractions, effacing, and dilating the cervix to facilitate natural delivery [14]. In France, the labor of 22.7% of women is artificially induced [15, 16], and the indications may be maternal, fetal, or obstetric. Labor induction rates are rising all around the world and are likely to continue increasing since the publication in 2018 of the randomized trial of Grobman et al. that found that there is a decrease in the risk of cesarean with labor induction at 39 weeks of gestation (WG) rather than expectant management [17].

Cervical ripening refers to cervical preparation prior to artificial labor induction [1]. Many studies use “artificial induction” to describe cervical ripening [18]. We will use both terms interchangeably, as cervical ripening is an integral part of artificial labor induction.

The induction process is evaluated using the Bishop score [19], which considers the length, dilatation, position, and consistency of the cervix and the height of the mobile fetus. The score predicts the success of term labor induction [20]. A score < 6 is considered poor. Some teams define a score ≤ 3 as very poor, 4–5 as rather poor, and ≥ 6 as good [21]. Some professionals advocate the use of objective cervical ultrasound [22, 23], but this practice remains controversial [24]. Other predictors of the success of induction include multiparity, higher gestational age (> 41 + 4 WG) [25], maternal age (< 35 years) [26], and body mass index (< 30 kg/m^2^) [27, 28].

The recommendations regarding cervical ripening differ in terms of the chemicals used, route of administration, dosage, and monitoring modality. Mechanical induction is employed in 50% of maternity hospitals [18]. The double balloon (Cook®) is a single-use device placed for up to 12 h. The Foley® catheter is a single balloon catheter (n°18), and the Dilapan® is a cervical dilator.

Hormones are commonly used to induce labor. Oxytocin, in combination with amniotomy, is employed if the cervix is considered favorable (Bishop score ≥ 6), reducing the interval between induction and delivery [29]. If the cervix is unfavorable, oxytocin is also used to trigger labor but is not the first choice [29]. Natural (Propess®, Prostine®, and Prepidil®) and synthetic (Misoone®, Gymiso®, Nalador®, and Cervagem®) PGs have been used since 1968 to induce cervical ripening if the Bishop score is < 6.

PGs are widely used in France [30]. The Propess®, a vaginal patch featuring progressive continuous diffusion of 10 mg dinoprostone (0.33 mg/h), is placed for 24 h. Propess® use has increased greatly over time, from 10.2% [30] of maternity hospitals in 2001 to 89.1% today [10].

Dinoprostone in various forms (Propess®, Prostine®, and Prepidil®) exhibits a very good risk-to-benefit ratio [7]. According to the Higher Health Authority, intravaginal forms should be favored if PGs are used to induce labor [1]. Furthermore, the Propess® can obviously be removed at any time if uterine hypertonia (which may trigger fetal repercussions) develops, unlike prostaglandin gels (Prostine® and Prepidil®), which cannot be removed.

The National Institute for Health and Clinical Excellence states that labor induction using PGs increases 24-h vaginal delivery rates and reduces the need for cesarean section and epidural analgesia. Also, the maternal satisfaction rate is higher than when oxytocin (alone or with amniotomy) is used to induce labor [8].

Of all French maternity hospitals, 75.6% deliver oxytocin infusions regardless of the cervical condition (favorable or not) despite the risk of a cesarean section in instances of failure [10]. One study found that 65.4% of nulliparous patients with a Bishop score ≤ 3 underwent cesarean section after induction with oxytocin and amniotomy; in 66% of these cases, induction failed [31]. Moreover, a nulliparous status combined with a very unfavorable Bishop score imparted a 50% risk of induction failure, which decreased to 10% if the Bishop score was 4–6. One study involving 995 patients compared the use of single versus double doses of a vaginal prostaglandin E2 (PGE2) gel (2 mg PG); neither the cesarean nor instrumental extraction rate differed. Application of two PGE2 doses in multiparous women reduced the need for amniotomy and oxytocin [32].

Antonazzo et al. (2016) published the only randomized trial (albeit low patient numbers) demonstrating that the vaginal delivery rate increased significantly after a second vaginal application of dinoprostone (26/47, 55.3%) compared with oxytocin (16/47, 34.0%, *p* < 0.05), without any increase in neonatal morbidity [13].

In our Obstetrics and Gynecology Department (Limoges University Hospital), a second Propess® is sometimes applied in the absence of labor if the cervix remains unfavorable. In 2014, 44 of 65 patients (67.7%) who received a second Propess® delivered vaginally.

The French Higher Health Authority has issued dosage recommendations for PGE2 tablets and gels but does not mention the intravaginal diffusion systems, despite its widespread use (in one or two Propess®).

## Methods

### Objective and primary outcome

Our principal objective is to determine if the first Propess® does not induce cervical ripening and whether a second Propess® (followed by oxytocin (Syntocinon®)) if necessary) increases the vaginal delivery rate compared with that after direct oxytocin (Syntocinon®) injection.

The vaginal delivery rate is thus the primary outcome.

### Objectives and secondary outcomes

The secondary objectives and outcomes of our study are as follows:
Comparison of induction failure (the absence of labor 24 h after placement of the second Propess® [cervical dilatation still < 3 cm]) between the test and control groups (cervical dilatation < 3 cm) despite 6 h of Syntocinon® infusion (one ampoule), amniotomy, and the presence of regular uterine contractions.Comparison of maternal morbidity and mortality between the test and control groups. We will record:
labor duration (time in minutes from attainment of 3 cm cervical dilatation to delivery),indications for cesarean section,all instances of instrumental extraction,maternal hospitalization duration,peri-delivery hemorrhage (> 500 ml) and its treatment,complete uterine rupture,transfer to intensive care units,death.Comparison of fetal morbidity and mortality between the test and control groups. We will record:
Apgar scores < 7 at 3, 5 min and < 9 at 10 min,fetal acidosis (umbilical arterial pH < 7.15 and < 7, lactate levels > 5, base excesses > 12),all instances of amniotic fluid containing meconium at birth,transfer to the neonatal intensive care unit,fetal/neonatal death.

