### Trial design

This is a multicenter, randomized, open-label, superiority trial with two parallel arms.

If labor has not commenced 24 h after placement of the first Propess®, patients will be asked to give written informed consent and then will be electronically randomized by a study investigator (doctor) to the control (oxytocin and peridural analgesia if the patient wishes) or experimental (a second 24-h Propess® prior to oxytocin if necessary and peridural analgesia if the patient wishes) group. Written informed consent will be obtained from all participants by a study investigator (doctor) before randomization.

Randomization (ratio 1:1) will be carried out centrally via the Center for Epidemiology, Biostatistics and Research Methodology (CEBIMER) computer platform (Ennov Clinical®) accessible 24 h a day, 7 days a week. To randomize a patient, the investigator must connect to the platform (secure connection) and after a phase of verification of the eligibility criteria, the randomization will be performed automatically.

The allocation will be performed by minimization, which provides similar distribution of selected factors between control and experimental groups. Randomization lists are not set up in advance and the first participant is randomly allocated. For each following participant, the treatment allocation that minimizes the mismatch on the five selected factors between groups will be identified.

It will be a randomization by minimization on the following factors:
Bishop’s score (< 3, 3–5),body mass index (< 30, ≥30 kg/m2)parity (nulliparous, multiparous)age (< 40, ≥ 40 years old)center

First, a draft randomization list will be established by the methodologist and validated by the data manager. Then, the final randomization list will be performed and will be kept securely by the CEBIMER.

The follow-up data will be collected up to 10 days from delivery. This is not a blind study because of the galenic differences and the different methods of administration of the two treatments. As the induction of labor is necessary and justified for medical reasons, it is not possible to administer placebo.

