### Interventions

In the control group, 5 IU of oxytocin will be diluted in 49 ml of physiological saline and will be started at 2.5 mIU/min, a flow rate of 1.5 ml/h with an increase of 2.5 mIU every 20 to 30 min up to 12 ml/h. In case of abnormal fetal heart rate or abnormal uterine contractions, oxytocin will be stopped momentarily. In case of induction failure (cervical dilatation remaining < 3 cm despite 6 h of oxytocin = 1 syringe and the presence of regular uterine contractions and amniotomy), the patient must have a cesarean section. In total, oxytocin is administered to induce labor for 6 h and then if the labor begins, oxytocin can be continued for one more syringe in case there is a lack of uterine contractions or labor stagnation.

In the experimental group, the second Propess® must be removed after 24 h or earlier if labor begins, or in case of abnormal uterine contractions, abnormal fetal heart rate or poor material tolerance. If oxytocin is needed in the experimental group after 24 h of the 2nd Propess®, it should be delivered in the same way as in the control group. If the labor does not begin (cervical dilatation remaining < 3 cm despite second Propess® + 6 h of oxytocin = 1 syringe and the presence of regular uterine contractions and amniotomy), the patient must have a cesarean section. In case the second Propess® falls off, a 2-h-long wait is tolerated. If labor does not start and if the fall occurred before 18 h of use, another Propess® should be inserted for a duration which should not exceed 24 h of cumulative exposure. In case it falls after 18 h of use, induction of labor should continue through oxytocin.

Both treatments will be labeled and supplied to the different centers and stored according to the manufacturers’ recommendations: between − 10 and − 20 °C for Propess® and between + 2 and + 8 °C for oxytocin. A regular temperature verification must be done to ensure the good conservation of the products. Antalgic medications are authorized. Only Risordan® and Natispray® are allowed to correct abnormal uterine contractions. No other medical or mechanical labor-inducing means are permitted.

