### Statistical analysis

Data will be analyzed by the UVEC (pharmacovigilance unit) for security and vigilance analyses and local CEBIMER for the main statistical analyses using SAS 9.3 (SAS Institute Cary, NC). *p* values < 0.05 will be considered statistically significant. Our analysis will be conducted using the intention-to-treat principle and reporting will follow CONSORT 2010 recommendations.

Descriptive statistics of continuous data will be reported as means ± standard deviations or medians and interquartile ranges depending on the distribution of the variable. Dichotomous and categorical data will be presented by numbers and percentages. The primary outcome will be reported with numbers and percentages in each group. The analysis of the primary outcome will be conducted by comparing the proportions of vaginal delivery between the two groups with the use of a Chi-square or Fisher’s exact test depending on the theoretical numbers. The effect seize will be estimated using odds ratio and its 95% confidence interval.

Secondary analyses will be computed in order to compare failure induction of labor, maternal and fetal morbimortality between the two groups of randomization by using a Chi-square or a Fisher’s exact test depending on the theoretical number for dichotomous or categorical outcomes and a Student’s *t* test or a non-parametric Mann–Whitney test for continuous outcomes depending on the distribution of the variable.

We will use the Shapiro–Wilk test for testing whether variables are normally distributed.

All data analysis will be performed unblinded according to a pre-established statistical analysis plan drafted prior to access to the data and reported in a document signed by all authors. This statistical analysis plan will be updated before data lock for the final analysis.

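### Induction failure is worded at a mid-strategy time point for the second-Propess arm but at the end of oxytocin for control, and this does not match the Interventions section

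*Protocol article*

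**What the plan says.** Objectives and secondary outcomes lists induction failure first and attaches two descriptions to it. After the second pessary it is "the absence of labor 24 h after placement of the second Propess® [cervical dilatation still < 3 cm"]. A second parenthesis, placed after the mention of the test and control groups, gives dilatation under 3 cm "despite 6 h of Syntocinon® infusion (one ampoule), amniotomy, and the presence of regular uterine contractions".

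The Interventions section gives the control arm the same criterion, calls it induction failure, and words it as "cervical dilatation remaining < 3 cm despite 6 h of oxytocin = 1 syringe and the presence of regular uterine contractions and amniotomy". For the test arm it uses a later point: "cervical dilatation remaining < 3 cm despite second Propess® + 6 h of oxytocin = 1 syringe", again with regular contractions and amniotomy.

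Trial design describes the test strategy as "a second 24-h Propess® prior to oxytocin if necessary", and the Abstract and the principal objective agree. Statistical analysis plans a chi-square or Fisher's exact test to "compare failure induction of labor, maternal and fetal morbimortality between the two groups of randomization".

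**The concern.** The trial compares two strategies, and oxytocin is the planned second step of the test strategy for women who need it. If the outcome list is followed as worded, a test-arm woman is classified when the pessary period ends, before that step. A control woman is classified after the oxytocin step. A test-arm woman who is under 3 cm at 24 h, then labors on oxytocin and delivers vaginally, would count as an induction failure. Part of any difference between arms would then come from the definition rather than the treatment.

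The article also holds two test-arm criteria that can give different counts. The trial is open-label and the analysis is described as unblinded, so the choice between them should be settled before outcome data are examined.

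**Working it through.** **The plan's own figure.** No rate or sample size is given for induction failure. The stated 176 per group concerns vaginal delivery (55% v 70%, two-sided 5%, 80% power). With mean proportion 0.625:

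n = [1.960·√(2·0.625·0.375) + 0.842·√(0.55·0.45 + 0.70·0.30)]² / 0.15² = 162.3, so 163 per group.

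The continuity correction, (n/4)·[1 + √(1 + 4/(n·0.15))]², gives 175.4, so 176. The stated figure is reproduced, and this point does not touch it.

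**The criteria side by side.**

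| Arm | Objectives and secondary outcomes, as worded | Interventions |
|---|---|---|
| Control | < 3 cm despite 6 h oxytocin, amniotomy, regular contractions | Same |
| Test | No labor, < 3 cm, 24 h after second Propess | < 3 cm despite second Propess and 6 h oxytocin, contractions, amniotomy |

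Only the test-arm row differs.

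**Direction.** Test-arm oxytocin is placed after the pessary period: "If oxytocin is needed in the experimental group after 24 h of the 2nd Propess". A woman still under 3 cm after 24 h of pessary and then 6 h of oxytocin was also under 3 cm at 24 h. Failures by the Interventions criterion are therefore a subset of failures by the outcome-list wording. Let u be the share of the test arm under 3 cm at 24 h, and g the share of those still under 3 cm after the oxytocin period. Then:

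- outcome list as worded: u
- Interventions criterion: u·g
- excess from the wording: u − u·g = u·(1 − g), which is positive whenever g < 1

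The control rate is the same under both sections.

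**Where the subset argument may not hold exactly.** If the second Propess is removed early, the rest of the strategy may be over before the 24 h point. If it falls out after 18 h of use, oxytocin follows, so a woman may already be on oxytocin at 24 h.

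**Size.** The documents give neither u nor g for this population. The values below are assumptions, used only to show how far the result depends on them. The 27% and 35% for u are 1 − 0.73 and 1 − 0.65, from the Background's labor rate after a first Propess; 50% is arbitrary. The 10% and 50% for g are the Background's failure risks for nulliparous women by Bishop score; 30% is a midpoint. The control failure rate is set equal to g.

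| u | g = control | Test minus control, as worded (u − g) | Test minus control, Interventions (u·g − g) | Excess u(1 − g) |
|---|---|---|---|---|
| 27% | 10% | +17.0 | −7.3 | 24.3 |
| 27% | 50% | −23.0 | −36.5 | 13.5 |
| 35% | 30% | +5.0 | −19.5 | 24.5 |
| 50% | 10% | +40.0 | −5.0 | 45.0 |

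All differences are in percentage points. The excess runs from 13.5 to 45 points, or 24 to 81 of 180 women. Setting control equal to g makes the Interventions difference negative by construction, so that column is no forecast. The table shows only that the two wordings can differ in sign for some inputs and not for others.

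**The case against.** The strongest reply is that the sentence in the outcome list is garbled and that its oxytocin clause, which follows the mention of both groups, is meant for both. Test-arm failure would then be the Interventions criterion, in line with the strategy described in the Abstract, the principal objective and Trial design. This reading is possible, and the authors may well have intended it. But the test-arm description stands in its own closed parenthesis with its own time stamp. Apart from early removal or fall-out, a woman assessed 24 h after placement cannot already have had 6 h of an infusion that starts after those 24 h. The two sections need reconciling under either reading.

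It is also fair to say that Interventions uses the term induction failure only for control; for the test arm it speaks of labor not beginning. The two criteria are parallel and have the same stated consequence, but treating the second as an outcome definition is an inference. The full protocol and the analysis plan are not shown and may be clearer.

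Three stronger readings are tempting, and the documents do not support them:

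- **Every test-arm woman who needs oxytocin is scored as a failure.** Oxytocin may also be continued once labor has begun, for weak contractions or stagnation. A woman already at 3 cm is not a failure under either wording. Early removal and fall-out are further exceptions.
- **The bias can be sized from the 65–73% labor rate in the Background.** That rate follows a first Propess, whereas these women are the ones in whom the first did not work. No figure is given for how many reach 3 cm on subsequent oxytocin.
- **The trial's main conclusion is at risk.** Vaginal delivery is defined without reference to this outcome.

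**Conclusion.** The point holds as an inconsistency in one secondary outcome, of moderate severity. As worded, the outcome list assesses the test arm before its planned oxytocin step and the control arm after it, and disagrees with Interventions. Taken literally, this can only raise the test-arm failure count, apart from possible exceptions after early removal or fall-out, and leaves the control count unchanged. The comparison is then biased against the second Propess by u·(1 − g). The direction needs only that some women under 3 cm at 24 h reach 3 cm on oxytocin. The size cannot be derived from the documents. Whether the bias would occur in practice depends on which reading the analysis follows, and the article does not settle that. The primary outcome and the sample size are unaffected.

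**What to change.** Reconcile the definition in Objectives and secondary outcomes with the Interventions section:

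1. State one definition of induction failure for both arms, assessed at the end of each assigned strategy.
2. Keep all randomized women in the denominator, in line with the intention-to-treat principle already stated.
3. State how women delivered by cesarean before completing the oxytocin period are classified, and how early removal or fall-out of the second pessary is handled.
4. Report the share of women not in labor 24 h after the second Propess for the test arm only, as a description and not as a between-arm test.

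This changes outcome wording in the protocol and analysis plan, not clinical management. The sponsor should confirm that the case report form records dilatation at the end of the oxytocin period; Interventions makes management depend on it, but the article does not say that it is collected. Trial status reports 110 of 360 women randomized on 22 October 2019, and the analysis plan is to be updated before data lock, so on the article's account the correction could still be made in time.

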### Sample size calculation

The number of participants is based on the primary outcome calculation for a comparative superiority test. Based on a local retrospective study (55% vaginal delivery rate after Propess® and 70% after two Propess® placements and Syntocinon®) performed prior to that of Antonazzo [13], the 15% between-group difference indicates that to afford an 80% power to detect a specific difference at the 5% significance level (two-sided test), 176 patients per group are required in a two-group scenario (nQuery Advisor 7). As the rate of non-evaluable patients (early drop-out, violation of inclusion or exclusion criteria, lack of compliance, intercurrent illness, comedication which was not allowed by the protocol) is expected to be very low in this study due to the nature of the primary outcome (vaginal delivery), we believe that a total of 360 (180 per group) will be an adequate sample size for the study.

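### Fetal acid-base outcomes are defined only as threshold events; adding a comparison of the measured cord pH and lactate would recover power against a general shift, at almost no cost

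*Protocol article*

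**What the plan says.** Under Objectives and secondary outcomes, the protocol article includes among the fetal morbidity items "fetal acidosis (umbilical arterial pH < 7.15 and < 7, lactate levels > 5, base excesses > 12". Each acid-base item is a threshold crossing. The same list defines labor duration on its own scale, in minutes, and includes the length of the maternal hospital stay, so some secondary outcomes are continuous by definition.

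The Statistical analysis section compares secondary outcomes with a "Chi-square or a Fisher’s exact test depending on the theoretical number for dichotomous or categorical outcomes", and with a Student's t test or a "non-parametric Mann–Whitney test for continuous outcomes depending on the distribution of the variable". It does not list which outcomes count as continuous. The significance rule is "values < 0.05 will be considered statistically significant". The section also refers to a separate statistical analysis plan, which is not shown.

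Under Sample size calculation, the trial is sized on vaginal delivery alone: "we believe that a total of 360 (180 per group) will be an adequate sample size for the study". No power is claimed for any fetal outcome.

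**The concern.** Umbilical arterial pH and lactate are laboratory values on a continuous scale. Nobody can be classed as below 7.15 or above 5 without the value itself, so the trial will already hold the full measurements. Reducing each to yes or no before comparing the arms discards information, and discards more the rarer the event.

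The experimental treatment is a second pessary used outside its marketing authorization, and fetal morbidity is one of the stated comparisons. A non-significant test on a handful of events says little about whether acid-base status moved moderately in one arm. A difference in the measured values with its confidence interval would show what size of shift the data exclude.

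**Working it through.** **Inputs from the article.** 180 per arm, 1:1 allocation, 5% level, two-sided. The two-sided level is stated for the sample size ("at the 5% significance level (two-sided test), 176 patients per group are required") and is assumed here for the secondary tests.

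**Assumed, because the article gives no figures.** Approximately normal values; a shift of d standard deviations between arms; a proportion p of control newborns beyond the cut, shown as a range.

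**Step 1: the article's own figure.** The design aims "to afford an 80% power to detect a specific difference" between 55% and 70%.
- Pooled formula: n = [1.960√(2·0.625·0.375) + 0.842√(0.55·0.45 + 0.70·0.30)]² / 0.15² = 162.3, so 163 per group.
- Continuity correction: (162.3/4)·[1 + √(1 + 4/(162.3·0.15))]² = 175.4, so 176 per group.

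The stated 176 is reproduced with the continuity correction. It concerns the primary outcome only.

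**Step 2: power when the values are compared.** For d = 0.3 the noncentrality is 0.3·√(180/2) = 2.85, and Φ(2.85 − 1.96) gives about 81%. Exactly 80% power corresponds to d = (1.960 + 0.842)·√(2/180) = 0.295. For d = 0.2 the power is 47%.

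**Step 3: power when the cut is tested.** A control rate p becomes p₂ = Φ(Φ⁻¹(p) + d) in the shifted arm. Example with p = 10% and d = 0.3:
- p₂ = Φ(−1.282 + 0.3) = 16.3%, a difference of 0.0632.
- The standard error is 0.0356 under the null and 0.0355 under the alternative.
- Power ≈ Φ[(0.0632 − 1.96·0.0356)/0.0355] = Φ(−0.19) = 43%.

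Exact binomial enumeration (uncorrected chi-square; Fisher where an expected count is below 5) gives the table for d = 0.3, except that the 50% row is the normal approximation at d = 0.295. The last column is 1 − power/81% (1 − power/80% for the 50% row).

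| Control rate beyond the cut | Power of the cut | Share of power lost |
|---|---|---|
| 50% | 60% | 25% |
| 25% | 58% | 28% |
| 15% | 50% | 38% |
| 10% | 43% | 47% |
| 5% | 31% | 62% |
| 1% | 5% | 94% |

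At 1% the uncorrected chi-square approximation gives 13% power at d = 0.295, a loss of 1 − 13/80, about 83%. Either way the loss exceeds four fifths.

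**Step 4: information kept.** For small shifts the cut keeps φ(z)²/[p(1 − p)] of the information, where z = Φ⁻¹(p): 0.54 at 25%, 0.34 at 10% and 0.07 at 1%. Multiplied by 180, this is worth about 97, 62 and 13 newborns per arm.

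**Step 5: a different pattern of harm.** Suppose 10% of the experimental arm is shifted by 2.5 SD and the rest not at all (1,500 simulated trials per setting, Monte Carlo error about 1.3 points at most).

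| Control rate beyond the cut | Chi-square on the cut | t test | Mann–Whitney |
|---|---|---|---|
| 10% | 59% | 56% | 33% |
| 5% | 75% | 55% | 33% |

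Here the cut is as strong as the comparison of values, or stronger.

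**The case against.** Four points weigh on the other side.

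- **The analysis plan may already do this.** The article is condensed, the statistical analysis plan is not shown, and t and Mann–Whitney tests are available for continuous outcomes. A reader might infer that pH and lactate will never be analysed as values. The documents do not say so: no such analysis is named, and none is excluded. What remains is that the outcome, as the article defines it, is a set of events.
- **The size of the loss is not known.** A reader might infer that most of the power is lost for all three cuts. The article gives no event rate for any of them. Under a shift of 0.3 SD, more than half of the power goes only when the control rate is below about 10%. That is plausible for pH < 7 but cannot be claimed for pH < 7.15 or lactate > 5.
- **Acidosis as an event is a different question from a mean shift.** The stated objective is fetal morbidity, and an event is closer to it. Step 5 shows that replacing the event tests could lower sensitivity to harm in a subgroup. This stands in full, and it rules out reducing the event counts to description alone.
- **Safety does not rest on this test.** An independent committee meets every 60 patients to look for excess morbidity and mortality, serious adverse events are reported, and no power is claimed for fetal outcomes. This limits the importance of the point but does not remove it.

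**Conclusion.** The point holds in a limited form. The article's outcome list and its test rules are consistent with each other, so this is not a contradiction. It is an outcome definition that leaves information unused. Under a uniform shift of about 0.3 SD with 180 per arm, testing the cut instead of the values costs between about a quarter and over four fifths of the power, depending on how common the event is. Those figures depend on normality, on a shift common to all newborns and on assumed control rates. With harm confined to a subgroup, the ordering can reverse. Neither analysis dominates, which is the reason to have both. The matter is minor: it concerns a secondary safety outcome and leaves the primary comparison untouched.

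**What to change.** In Objectives and secondary outcomes, and in Statistical analysis, add a between-arm comparison of measured umbilical arterial pH and of measured lactate as supportive secondary safety analyses. Report the mean difference with its 95% confidence interval or, if the values are skewed, a Mann–Whitney test with the Hodges–Lehmann shift and its interval. Keep the planned event comparisons for pH < 7.15, pH < 7 and lactate > 5, and give them confidence intervals too. If the statistical analysis plan already contains the continuous comparison, it is enough to align the outcome definition with it.

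The cost is a sentence or so of text and a few lines of analysis, with no new patients or measurements. The downsides are two more secondary comparisons and a result, a shift in the mean, that is less directly clinical than an event.
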